#### Economic and impact evaluation

Infectious disease models can test the extent to which observed changes in disease transmission can be attributed to specific interventions,^108–112^ and assess cost-effectiveness of interventions that avert secondary infections, that is, have a population prevention benefit.^50 85 113–117^ We will update and adapt a transmission model of HCV among PWID in Scotland and Tayside to model the impact of the HCV treatment intervention based on historical trends and new observations collected as part of this programme.^39 87^ We will stratify the PWID population into current (injected in the previous year) and temporarily ceased (in OST and not injected in the previous year); as well as by duration of injecting (<3 years, 3 to 9 years, 10+years since onset), prevention intervention exposure (OST and/or high coverage NSP), and intervention settings for testing and treatment. We will use Approximate Bayesian Computation to calibrate the model to pre-intervention trends in chronic HCV prevalence and incidence among PWID in Tayside. The model will simulate the impact of observed rates of HCV treatment and cure rates for the intervention period, also incorporating any changes in the coverage of OST and NSP and injecting risk behaviours.

We will test consistency between the model impact projections and observed changes in HCV chronic prevalence and incidence from Tayside to disentangle the impact of HCV TasP from other interventions (OST/NSP) or epidemiological changes, and predict the impact of the TasP on number of HCV infections averted. If they are not consistent then alternative evidence-based hypotheses will be tested for why the model projects a different impact and the best fitting models will then be used to project the impact of the intervention. This will be assessed compared with two alternative counterfactuals where treatment rates are either at pre-scale-up levels in Tayside or at the average level achieved in other UK sites over the scale-up period. The impact of any changes in OST and NSP coverage will also be assessed to determine the contribution of those changes on observed effects. Impact will be assessed in terms of the relative decrease in prevalence and incidence, as well as the number and per cent of infections averted in the intervention model projections compared with each counterfactual over different time frames. These model projections can also be taken forward to evaluate the possible impact of the intervention over next 5 or 10 years.

We will evaluate the cost-effectiveness of the intervention (HCV treatment scale-up) compared with status quo (expected rate of HCV case-finding and treatment among PWID in the rest of the UK) from a healthcare provider (NHS) perspective, with the cost-effectiveness of the different settings where case-finding occurs also being assessed. The cost-effectiveness model will be based on the same dynamic impact model, adapted to include HCV disease progression stages and tracking of health outcomes among PWID after cessation of injecting.^50^ The economic evaluation will incorporate both individual benefits of HCV treatment (on disease progression) as well as population benefits (on HCV transmission). We will calculate the total number of infections and deaths over a 50 year time horizon for the intervention and counterfactual scenario and estimate the costs and quality-adjusted life years (QALYs) based on the number of individuals in each disease stage per year in the model. We will discount all future costs and QALYs at 3.5% (The National Institute for Health and Care Excellence (NICE) guidelines https://www.nice.org.uk/process/pmg9/resources/guide-to-the-methods-of-technology-appraisal-2013-pdf-2007975843781). Probabilistic sensitivity analyses will be used to estimate the parametric uncertainty in the impact and cost projections. Cost-effectiveness results will be expressed in terms of incremental cost-effectiveness ratios and net monetary benefits estimated using NICE thresholds (£20 000 and £30 000 per QALY). We will plot cost-effectiveness acceptability curves to determine the probability of the intervention being cost-effective compared with different willingness-to-pay thresholds. Analyses of covariance methods will be used to summarise the proportion of the variability in the incremental costs and QALYs explained by uncertainty in different input parameters. Univariate sensitivity analyses will consider the effect of changes in important parameters such as time horizon, treatment cost and discount rate.

We focus on the incremental or additional resource costs associated with the intervention in Tayside. These costs, in part based on our earlier work for other studies, will include such things as the nurse time spent on intervention related activities (training other staff to offer HCV testing and treatment referral) as well as additional HCV testing and treatment costs, any additional OST costs due to HCV testing or treatment, and other staff time at the NSP, drug treatment centres and prisons involved with the intervention. Most of the incremental costs can be defined as variable (driven by extra nurse time and HCV testing/treatment costs). NHS HCV care costs and health utilities will be attached to each disease stage, based primarily on previous syntheses and models, which assume that PWID have a lower quality of life (QoL) than non-PWID of a similar age, gender and liver disease stage.^118–120^ Additional data using the EQ-5D-5L tool during this study will generate new health utility data on the QoL among PWID before and after DAA treatment.

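### After a mismatch, the impact estimate comes from models selected on the same post-intervention data, and the stated intervals cover parametric uncertainty only

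*Protocol article*

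**What the plan says.** All the relevant text is in the protocol article under Economic and impact evaluation.

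- **Calibration.** Approximate Bayesian Computation is used to "calibrate the model to pre-intervention trends in chronic HCV prevalence and incidence among PWID in Tayside".
- **Projection.** "The model will simulate the impact of observed rates of HCV treatment and cure rates for the intervention period". Changes in OST and NSP coverage and in injecting risk are also included.
- **Check.** "We will test consistency between the model impact projections and observed changes in HCV chronic prevalence and incidence from Tayside". Its purpose is "to disentangle the impact of HCV TasP from other interventions (OST/NSP) or epidemiological changes".
- **If the check fails.** "If they are not consistent then alternative evidence-based hypotheses will be tested for why the model projects a different impact". As the step after that, the article says that "the best fitting models will then be used to project the impact of the intervention". Impact is then measured against two counterfactuals: treatment at the Tayside level before scale-up, or at the average of other UK sites.
- **Uncertainty.** "Probabilistic sensitivity analyses will be used to estimate the parametric uncertainty in the impact and cost projections". The univariate sensitivity analyses also vary parameters.
- **Downstream use.** "The cost-effectiveness model will be based on the same dynamic impact model".

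**The concern.** As long as the model has seen only pre-intervention data, agreement between projection and observation is evidence. The model could have been wrong and was not. Once the observed prevalence and incidence have been used to choose among revised models, agreement is what the selection was for, and it no longer tests whether treatment caused the change.

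Two consequences follow. First, a reader who is shown only the revised models could take their good fit as confirmation. Second, several revisions may fit about equally well and still imply different treatment effects. A parametric analysis within the chosen models does not by itself show that spread.

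The outputs at stake are infections averted and the cost-effectiveness results over 50 years. The Discussion says that the no-scale-up counterfactual for cost-effectiveness has to come from this transmission model, so no other source for it is given.

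**Working it through.** **Reading the steps in order**

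1. The calibration data are pre-intervention, and the intervention-period inputs are observed treatment, cure, OST/NSP and risk behaviour. The first comparison is therefore out of sample.
2. The misfit is defined against post-intervention Tayside prevalence and incidence. The article names no other data on which the later models could be best fitting, so selection on those same data is the natural reading. It is an inference, because the article does not describe free refitting.
3. The selected models supply the impact projection. The cost-effectiveness model is built on the same dynamic model.
4. The uncertainty analysis named for impact and cost is parametric. Differences between models are not mentioned.

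The article gives no figure of its own to reproduce for this point.

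**Illustration: can models that match the same prevalence differ in impact?**

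Inputs from the article: N = 2760 PWID; 26% chronic prevalence; incidence 4.2 per 100 person-years; 66 treatments per year before 2017; 500 over two years, taken as 250 per year; cure 0.90, the floor of the stated range.

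Assumptions made here: one susceptible/infected compartment, a baseline in equilibrium at 66 treatments per year, and the observed values tried below. This is not the trial's model.

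- Infected at start: 0.26 × 2760 = 717.6. Susceptible: 2042.4.
- Transmission coefficient: 0.042 / 0.26 = 0.1615 per year.
- Exit rate for equilibrium: (0.042 × 2042.4 − 66 × 0.90) / 717.6 = (85.8 − 59.4) / 717.6 = 0.0368 per year.
- Dynamics: dI/dt = 0.1615 × m × S × I / N − 0.0368 × I − (treatments per year) × 0.90 × e. Here m multiplies transmission and e is the share of treatments acting on the modelled pool.

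With m = e = 1, prevalence falls to 13.3% at year 2 (the article's own model projects 10%). Infections over two years are 171.6 at 66 treatments per year and 140.4 at 250, so 31.2 are averted.

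Now suppose a higher prevalence is observed at year 2. Solve either for e (revision A) or for m (revision B), and count infections averted against 66 treatments per year, the article's pre-scale-up counterfactual:

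| Assumed observed prevalence | A: e | B: m | Averted, A | Averted, B | B / A |
|---|---|---|---|---|---|
| 14% | 0.962 | 1.12 | 29.2 | 34.4 | 1.2 |
| 16% | 0.847 | 1.46 | 23.8 | 43.3 | 1.8 |
| 18% | 0.731 | 1.79 | 18.6 | 50.7 | 2.7 |
| 20% | 0.615 | 2.09 | 13.6 | 56.7 | 4.2 |

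At 18%, the prevalence effect is 26.0 − 18.0 = 8.0 points under A and 31.4 − 18.0 = 13.4 points under B, because B raises the counterfactual prevalence to 31.4%.

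**Do A and B also agree on incidence?** No. At year 2, incidence is 0.1615 × m × prevalence. For the 18% case, A gives 0.1615 × 0.18 = 2.9 and B gives 0.1615 × 1.79 × 0.18 = 5.2 per 100 person-years. The article compares incidence as well as prevalence, so its check could in principle tell them apart. Whether it could in practice depends on how many recent infections the Tayside samples yield, which the article does not state.

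**The case against.** **The check can fail.** A reader might infer from the rule that the attribution check cannot fail. The text does not support that. The first comparison is out of sample, and the rule opens by providing for inconsistency. A revised model may also give treatment a smaller share. This objection stands.

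**Rival explanations are not tried only on misfit.** One might read the rule as one-sided. However, OST/NSP and risk-behaviour changes enter the main run, and the contribution of OST/NSP changes is to be assessed with no condition on fit. This stands too.

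**Attribution does not rest on this model alone.** The effect on prevalence and incidence is estimated separately by the Causal Impact synthetic control analysis, which does not use the transmission model. This also stands.

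**The wording is plural, the alternatives must be evidence-based, and the article is condensed.** The plural leaves room to carry several models, and the demand for evidence limits arbitrary refitting. The definition of consistency and the weighting of fits may sit in a fuller plan, and their absence is not held against the article. Even so, the selection step is stated here. Demanding evidence restricts selection on the outcome but does not remove it, and the uncertainty analysis named for these projections is parametric.

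**The illustration is not the protocol's comparison.** It matches prevalence at one time point only. Both revisions also alter quantities that the plan feeds in as observed. A requires that some treatments fall outside the modelled pool, and B requires a rise in transmission that the risk-behaviour data miss. This stands, so the ratios show what is possible and do not measure the problem.

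**Conclusion.** The point holds in limited form. If the projection and the data disagree, the impact estimate comes from models selected on the data that showed the disagreement. It is then a description that fits, and it cannot be counted as independent confirmation that treatment caused the change. Intervals that reflect parametric uncertainty alone would be too narrow to the extent that acceptable models disagree.

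That extent cannot be computed from the article. The 1.2- to 4.2-fold range above rests on a one-compartment model, assumed observed values and a match on year-2 prevalence only. If incidence discriminates well, the real spread could be much smaller.

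The outputs affected are the model-based impact, infections averted and cost-effectiveness. The synthetic control estimate is not touched. If the first comparison is consistent, the selection problem does not arise.

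A reader might also infer that attribution should rest only on the locked model, even when it misfits. That does not follow. Understanding and repairing a misfitting mechanistic model is reasonable, provided the results are labelled for what they are.

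**What to change.** 1. Keep the model calibrated to pre-intervention data fixed. Report its predicted-versus-observed comparison, infections averted and cost-effectiveness whatever the fit.
2. Present any revised models beside it, labelled as selected on the outcome data.
3. Carry all revised models that fit both prevalence and incidence acceptably into the impact and cost intervals, against the two counterfactuals already specified. Approximate Bayesian Computation weights are one way to do this, since that method is already planned for calibration.

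The cost is extra model runs, some added wording, wider intervals and two sets of results to explain. No new data are needed.

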### Patient and public involvement

Patient and public involvement (PPI) was led by the Hepatitis C Trust and supported by qualitative research assessing barriers and facilitators to HCV treatment access (led by [name]). The SDF were also actively involved in the development of EPIToPe. The input from PPI groups has influenced the design of care pathways and has ensured that peer research is an essential element of the qualitative strand of EPIToPe.

A pilot National Institute for Health Research (NIHR) funded study in England (HEPCAT) responding to NICE Guidance on Hepatitis Case Finding was co-designed with Hepatitis C trust. It showed that Hepatitis C Facilitators and peer-support networks can increase the uptake of HCV case-finding and HCV treatment readiness in addiction services. This pilot study and our studies in Dundee/Tayside will influence how HCV treatment can be scaled up in England and our proposed evaluation HCV treatment as prevention.

Peer researchers will be trained to conduct the longitudinal study with PWID treated for HCV and will be involved and contribute to the analysis of the findings. Peer researchers and SDF will be members of the project management group and steering committee.

Dissemination events will be held in Dundee to discuss and present the findings from the qualitative studies with patient groups and services. These will be facilitated by SDF to support active contribution from our peer researchers. The study findings will be summarised and promoted through SDF website, social media platforms and through their sector-wide conferences in Scotland. Hepatitis Scotland, who are hosted within SDF, together with patient and public groups in England will take an active role in the wider national and international dissemination of the research, it’s translation into patient meaningful materials and its integration into a national policy context. The research will also be promoted via Hepatitis C Trust and Public Health England.

## Discussion

### Strengths and limitations of this study

Several limitations arise from the ‘natural experiment’ design as our intervention and controls were not randomised. In the UK and many other countries there is no longer sufficient equipoise in clinicians and policymakers – given WHO and national strategies on HCV ‘elimination’ – to mount an randomised controlled trial of HCV TasP. As a result, there will be confounding and additional uncertainty in the measurement of the intervention effect. However, we consider that a natural experiment and use of synthetic control methods to be a more robust design than simple before and after studies. Our preliminary simulation work also suggests that we should have sufficient power to detect the large intervention effect that is planned.

We know also that HCV treatment and prevention strategy in UK (and Europe) is evolving – motivated both by WHO ‘elimination targets’ and falling drug prices – and our control sites in Scotland and England may increase HCV treatment rates earlier than expected. This will complicate the analyses a little and potentially dilute the intervention effect. We are confident that we can adapt the synthetic control methods to take account of changes over time – and that because Tayside has started so early in scaling up HCV treatment that we will have time to detect a difference in the outcome.

The lack of randomised controls means that we have to generate the counterfactual of ‘no HCV treatment scale-up’ through our HCV transmission model so that we can subsequently estimate cost-effectiveness of the intervention in Tayside. This is not ideal but has become standard practice in economic models of novel HCV treatment interventions – and we are involved with the modelling of HCV treatment pathways through homeless centres, prison, Accident and Emergency (A&E), pharmacies, specialist drug clinics and NSPs ([name] personal communication and for example^55 85 121^). We know also, however, that the benefit in terms of additional Quality of Life Years and averted HCV infections accrues and occurs over a prolonged period.^50^ It is more critical for any economic evaluation of HCV interventions in PWID that a dynamic model is used so that the prevention benefit (in terms of HCV infections averted) is correctly accounted for.

We are using peer researchers in the qualitative arm of patients’ perspectives on the intervention and on the impact of HCV treatment on addiction outcomes. This is novel but adds additional challenges to obtaining NHS passports and ensuring data quality across the interviews and interviewees. We are also intending to support peers in analysis and interpretation of the findings which we believe has not been done before. We have trained the interviewers and will be monitoring their performance of the interviewers to ensure consistent study quality – and will replace peers with our qualitative researcher if required.

### Future study: natural experiment of TasP in England

In England HCV treatment is delivered through 22 operational delivery networks (ODNs). NHS England’s HCV strategy (2016 to 2019) prioritised 10 000 patients per year in line with the declared priorities of the network which could (and in many cases did) include people who use drugs at risk of transmission.^44^ In October 2018 it is anticipated that a new procurement deal will substantially increase the number of patients who can access DAAs and this will enable ‘trace and treat’ options to be introduced. We will use the first part of EPIToPe including the manual generated by the qualitative study, enhancements to historical and ongoing surveillance of chronic HCV in PWID, infectious disease models and methodological developments of causal impact model, to co-design with ODN leads a natural experiment of HCV TasP in England.
